##### Statistical analysis

The analysis will be performed as an intention-to-treat analysis. No interim analysis will be conducted. Data validity will be conducted prior to analysis and corrected as appropriate.

The study population will be described separately for the two randomised groups using variables obtained at baseline. The variables will be described as mean (SD) and numbers (%) as appropriate.

The primary analysis of the primary outcome will be conducted using t-tests of independent group mean differences in 6MWT. The mean difference and 95% confidence interval will be reported and illustrated graphically. Individual change in 6MWT will be calculated from baseline and compared at different time points using t-tests.

The secondary analysis of the primary outcome will use mixed-level analysis with intervention group, time point and interaction of intervention and time points. This analysis will include baseline score for the outcome measure as a covariate. The estimated parameter for the interaction variables will be interpreted as the difference-in-difference between the two groups over time. A separate analysis will explore potential differences in the intervention group between participants who received the intervention at a training centre and those who trained at home. This analysis will be expanded to include descriptive baseline variables such as sex and age. The secondary analysis will use mixed-level analysis and include baseline score and baseline characteristics as covariates.

The cost-effectiveness analysis will be conducted from a societal perspective over the duration of the trial period. No extrapolation of long-term economic outcomes is planned. The EQ-5D-5 L data reported at each time point will be used to estimate quality-adjusted life years using time-weighted utility scores. The utility scores will be calculated for each individual at each data point using the Irish scoring algorithm for EQ-5D-5 L [47]. The area under the curve denotes the QALY, and incremental QALY is determined as the mean group difference.

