##### Missing data

Participants with missing data either because of early drop-out, loss to follow-up or missed participation in the data collection can bias the results. By design, no data will be missing at baseline because only participants with complete baseline data will be randomised.

Missing variables in outcome measures will be handled according to instrument developers’ guidelines. As a general rule, if more than 20% of the items of an instrument are missing, the summary score will be assigned as missing. Missing data will be reported as part of the summary presentation of the raw data. Logistic regression will be used to explore whether participants with missing data have different characteristics than the completers or whether missing data can be assumed missing by random.

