	20c	Participants with missing data, because of early drop-out, loss to follow-up or missed participation in the data collection, can bias the results. By design, no data will be missing at baseline because only participants with complete baseline data will be randomised. Missing variables in outcome measures will be handled according to instrument developers’ guidelines. As a general rule, if more than 20% of the items of an instrument are missing, the summary score will be assigned as missing. Missing data will be reported as part of the summary presentation of the raw data. Logistic regression will be used to explore whether participants with missing data have different characteristics than the completers or whether missing data can be assumed missing by random. If a pattern in missing data can be observed, missing data will be handled using “multiple imputation” techniques where missing variables are predicted in multiple dataset using descriptive variables identified as important covariates for missing data (sex, age, intervention group and baseline score).	19

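### Imputation of missing 6MWT depends on a pattern check that cannot establish missing at random, and the primary t-test has no stated handling if no pattern is seen

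*Protocol article*

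**What the plan says.** - **Trigger.** Table 2, item 20c: "Logistic regression will be used to explore whether participants with missing data have different characteristics than the completers". The same sentence also treats this regression as a way to judge if a missing-at-random assumption is tenable. The rule that follows is: "If a pattern in missing data can be observed, missing data will be handled using" multiple imputation. The item does not define a pattern and does not say what happens if none is seen.
- **Imputation predictors.** The same item lists "important covariates for missing data (sex, age, intervention group and baseline score"). The post-NCT 6MWT, scheduled for everyone in Table 1, is not among them.
- **Main text.** The Missing data section describes the same regression, with the stated purpose of finding out "whether participants with missing data have different characteristics than the completers or whether missing data can be assumed missing by random", but stops there. It has no imputation step.
- **Primary analysis.** Statistical analysis section: "The primary analysis of the primary outcome will be conducted using t-tests of independent group mean differences in 6MWT"; and "The analysis will be performed as an intention-to-treat analysis". Table 2, item 20a, repeats the t-test.
- **Secondary analysis.** "The secondary analysis of the primary outcome will use mixed-level analysis with intervention group, time point and interaction", with the baseline score as covariate (Statistical analysis; Table 2, item 20b).

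**The concern.** The regression is asked to do something it cannot do. It relates missingness to variables that were observed. A clear association counts against missing completely at random. A null result does not show missing at random, because the unobserved pre-surgery 6MWT is not in the model.

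Using the check as a gate adds a second problem. At this sample size, absence of a visible pattern is weak evidence that there is none, yet that is when imputation is not invoked. A t-test needs an observed value, so the primary result would then rest on participants who completed the pre-surgery test.

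A third problem arises when the gate opens: the imputation model leaves out the scheduled measurement closest to the endpoint.

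The plan itself anticipates 20% loss, and its background says that neoadjuvant treatment reduces fitness. Patients who walk poorly after that treatment may well be those who miss the pre-surgery test. If this selection differs by arm, the primary estimate is biased.

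**Working it through.** **Scale of the primary comparison.** Inputs: baseline 450 m, SD 85 m (Table 2, item 14); 15% difference, p = 0.05, power 80%, 26 with full data (read as per group), 20% drop-out, 62 recruited (Sample size calculation). Two-sided testing is assumed.
- Target difference: 0.15 × 450 = 67.5 m; standardised 67.5/85 = 0.794.
- A two-sample t-test needs 25.9, so 26 per group; power at 26 is 80.2%. The plan's figure reproduces.
- Expected missing outcomes: 0.20 × 62 = 12.4.

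**Power of the check.** Simulated logistic regression of missingness on arm, baseline score, age and sex, N = 62, 20% missing, about 2,000 runs per setting. The criterion is p<0.05 for the relevant coefficient. The criterion and the odds ratios are assumptions.

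| True pattern | Power |
|---|---|
| OR 1.5 per SD of baseline | 21% (23% in a separate simulation) |
| OR 2 per SD of baseline | 49% (53%) |
| OR 3 per SD of baseline | 83% |
| OR 2 / 3 / 4 between arms | 17% / 30% / 48% |

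An overall 4-df likelihood-ratio test gives 15–37% for all of these except OR 3 per SD of baseline, where it gives 70%.

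For 10% v 30% loss with 31 per arm:
- null SE = √(2 × 0.2 × 0.8/31) = 0.1016;
- SE under the alternative = √((0.1 × 0.9 + 0.3 × 0.7)/31) = 0.0984;
- power = Φ((0.20 − 1.96 × 0.1016)/0.0984) = Φ(0.01) ≈ 50%. Simulation gives 47%.

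**Bias if only completers are used.** Assumptions: no true effect, SD 85 m, correlation r = 0.7 between 6MWT measurements, about 20% missing, and missingness driven by the standardised post-NCT 6MWT, z. Then

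bias = r × 85 × (E[z | observed, exercise] − E[z | observed, control]).

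For logit P(missing) = −1.95 − 1.5z (OR e^1.5 ≈ 4.5 per SD lower), 19.6% are missing and numerical integration gives E[z | observed] = 0.222. With the intercept set for 20% missing, slope 0.75 gives 0.138 and slope ln 2 gives 0.129.

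| Mechanism | Formula | Simulation |
|---|---|---|
| Same selection in both arms | 0 m | 0.4 m |
| Half the slope in controls | 0.7 × 85 × (0.222 − 0.138) = 5.0 m | about 6 m |
| OR 2 per SD, exercise arm only | 0.7 × 85 × 0.129 = 7.7 m | about 7 m |
| OR 4.5 per SD, exercise arm only | 0.7 × 85 × 0.222 = 13.2 m | 13.0 m |

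In the last row, using group and baseline only leaves about 4 m. Adding post-NCT 6MWT leaves about 0 m. Varying r from 0.5 to 0.85 moves the completers' bias in that row from 9 to 16 m. A logistic check on arm and baseline is significant in only 17–33% of these trials.

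**Size against noise.** With 49.6/2 = 24.8 completers per arm, the SE of the difference is 85 × √(2/24.8) = 24.1 m. A 13 m bias is about half an SE and 13/67.5 = 19% of the target. In simulation it raised the t-test's false-positive rate to about 9%.

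**The case against.** Several points on the other side are sound.

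- **A suitable model is already planned.** The mixed model of the same outcome is unconditional. Fitted by likelihood, it would use the post-NCT 6MWT of participants who miss the pre-surgery test. A reader might infer from the imputation list that the plan never uses that measurement; this is not so. What stands is that the model is secondary, so it does not protect the primary result.
- **The completers' default is implied.** Nothing states what happens if no pattern is seen, and a fuller protocol or analysis plan might. The fallback follows only because a t-test needs observed values. The conditional rule itself, however, is written down, so the point concerns a rule fixed badly and not detail left out.
- **Intention-to-treat.** A reader might infer that the plan contradicts its own statement. It does not, because that statement can mean analysis by allocated arm. The plan simply leaves randomised participants without a pre-surgery 6MWT uncovered by any unconditional rule.
- **The check is not blind.** A reader might infer that it will usually find nothing. Power near 50% for some moderate patterns and 83% for a strong one does not support that, and the plan sets no significance threshold.
- **The 13 m figure is an extreme setting.** It needs strong selection in the exercise arm and purely random loss in controls. The argument that declining patients miss the test applies to both arms, and equal selection gives almost no bias.

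**Conclusion.** The concern holds in a limited form. The gate is unsound in logic whatever the numbers: a regression on observed characteristics cannot establish missing at random, and not seeing a pattern is no ground for skipping imputation. At N = 62 its power is low to moderate for moderate patterns, if p<0.05 is the criterion. When the gate does open, the predictor list omits the most informative scheduled measurement.

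The effect on the primary estimate is uncertain. Under the stated assumptions (SD 85 m, r = 0.7, about 20% missing, loss driven by poor post-NCT walking, no true effect), the bias is about 0 m with equal selection, about 5 to 8 m in intermediate settings, and about 13 m with strong selection in the exercise arm only. The correlation and the missingness mechanisms are not in the documents. Confidence is high on the logic and only moderate on the size. The change should be made, but the documents do not show that the primary result will be materially biased.

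**What to change.** Remove the pattern condition from Table 2, item 20c. For the primary comparison at the pre-surgery timepoint, specify one of these unconditionally:

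1. the already planned mixed model, fitted by likelihood to all randomised participants, with baseline 6MWT as covariate and post-NCT 6MWT among the repeated outcomes, reporting the group difference at the pre-surgery timepoint; or
2. multiple imputation whose model includes group, baseline 6MWT and post-NCT 6MWT.

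Keep the logistic regression as description only. Align the main-text Missing data section with item 20c, since only the latter mentions imputation. A delta-shift sensitivity analysis for data missing not at random would be a useful option, but its absence here is not a defect.

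The cost is wording and a little more analysis. All the variables are already collected, and visits and recruitment are unaffected.

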**Methods: monitoring**			
Data monitoring	21a	Data are monitored after the first complete patient at each site to ensure high-quality data. Data will be double data entered, and data validation will take place according to the procedures set out in the data management plan and data validation plan. Prior to any statistical analysis, all variables will be checked for the number of missing values, impossible values and improbable values. Impossible and improbable values will be defined by clinical opinion. Improbable values will also include values that are outside three standard deviations of the mean value. Any questions regarding the data will go back to the data manager. Descriptive statistics will be calculated for all variables, and distributional assumptions will be checked.	20
	21b	No interim analysis will be conducted.	18
Harms	22	Adverse events will be recorded in the relevant case report form by the researcher. Fatal or life-threatening serious adverse events are reported within 24 h of the research team becoming aware of the event. The serious adverse events form documents the nature of the event, date of onset, severity, corrective therapies given, outcome and causality (i.e., unrelated, unlikely, possibly, probably, or definitely). Queries relating to adverse event reporting will be directed to the chief investigator in the first instance.	17
Auditing	23	Complete compliance will occur with any auditing processes required by sponsor.	17
**Ethics and dissemination**			
Research ethics approval	24	Beaumont Hospital Ethics (Medical Research) Committee REC Ref: 18/58 Dublin City University Research Ethics Committee Ref: DCUREC/2018/255 University Hospital Galway Clinical Research Ethics Committee Ref: C. A 2160 Mercy Hospital Cork CREC Review Reference Number: ECM 4 (mm) 19/04/19 Waterford Institute of Technology REF:WIT2019REC0011	24
Protocol amendments	25	All site leads will be contacted by telephone if a significant amendment is made to the protocol. The amended protocol will then be emailed to all site leads.	
Consent or assent	26a	The study will be discussed with patients after their initial diagnosis is known but before neo-adjuvant treatment has started. No patient will have the study discussed with them on the day that they find out their diagnosis. Potentially eligible patients will have the study discussed with them by the principal investigator, or a nominated senior non-consultant hospital doctor at their next OPD appointment. Interested patients will receive an information leaflet and consent form for the study. After a period of 72h, patients will be contacted by telephone to confirm their interest in the study. Consent forms will be signed at their patient visit.	25
	26b	Additional explicit consent will be sought for collection and use of participant data and biological specimens in ancillary studies.	25
Confidentiality	27	Data will be entered with all direct patient identifiers removed; patients will be identified by study codes. All physiological data are held in an encrypted format. All data will be stored on a secure password protected desktop in a secured locked room.	20
Declaration of interests	28	The authors declare that they have no competing interests	25
Access to data	29	The data will only be accessed by the designated members of the research team.	
Ancillary and post-trial care	30	After the trial, the structured exercise classes will continue, and participants may continue to use the facilities.	
Dissemination policy	31a	The results will be published in peer-reviewed journals and disseminated at conferences and scientific meeting internationally. The findings of the trial will also be published in patient information magazines and booklets as informed with the help of the patient public involvement group.	
	31b	Authorship eligibility guidelines will be discussed and agreed with all contributors prior to publication, and the use of professional writers is not intended.	
	31c	No plans exist to grant public access to the full protocol, participant-level dataset, and statistical code.	
**Appendices**			
Informed consent materials	32	Model consent form and other related documentation are given to the participants and authorised surrogates.	
Biological specimens	33	Plans for collection, laboratory evaluation, and storage of biological specimens for genetic or molecular analysis in the current trial and for future use in ancillary studies, if applicable. (Not applicable)	

## Discussion

Exercise programmes can impact the outcomes of patients undergoing neoadjuvant therapy and surgery for oesphagogastric cancers in a variety of ways. They appear to improve patient functional status, HRQoL and, possibly, peri-operative morbidity [20]. Functional capacity may significantly improve during NCT when a prehabilitation programme is instituted [46, 48–54]. The use of exercise interventions and their timelines are inconsistently reported in the published literature as are the associated outcome measures that have included maximal inspiratory pressure [48–50], 6MWT [46, 52], gait speed [53], FEV1/FVC [51], VO2max and hand grip strength [49, 50]. The heterogeneity in the reported outcomes clearly makes it difficult to compare outcomes between studies. The PERIOP-OG trial aims to address this heterogeneity by including a number of outcome measures to examine cardiorespiratory fitness as well as physical strength. This will provide simple, easily reproducible measures of physical fitness that require minimal specialist equipment and can be widely reproduced in future comparable studies.

Within this trial, patient outcomes are comprehensively recorded during NCT, hospitalisation for resectional surgery and during post-operative recovery. Although the trial is not powered to investigate morbidity as a primary outcome, it may yield some insights as to the effect of the prescribed PERIOP-OG exercise programme on patient morbidity before, during and after surgery.

Quality of life and psychological outcomes are central to improving patient tolerance of NCT and oesophagogastric resection. Both also are recognised to be of increasing importance in survivorship. To date, there has been limited focus on whether exercise prescription can impact these outcomes. Most of the available data in this area are derived from post-operative rehabilitation interventions, which includes patients who may be a number of years from their surgery [19, 55, 56]. The PERIOP-OG trial includes multiple validated measures of patient outcomes, including the LOT-R, EQ-5D-5, FACT-E, GSE, PMS, SFQ, in addition to semi-structured interviews exploring patients’ experience of their peri-operative and surgical pathway. This will provide a comprehensive overview of the influence of this exercise intervention on psychosocial outcomes both before surgery and then after surgery as patients enter recovery and survivorship.

Importantly, any exercise interventions must not impact nutritional status. Specialised multidisciplinary input is available in all participating centres, with dedicated dieticians being involved in each patient’s care and with frequent measures being taken of BMI and nutritional status.

Ideally, all patients would attend supervised training exercise sessions. This is not feasible given the multi-centre nature of this trial, and the geographical distribution of patients. In an effort to maximise gym utilisation and the CBEP, providers will be trained in delivering the PERIOP-OG programme at multiple sites nationwide. This will reduce patients’ commute times and will improve compliance with interventions. For those unable to attend routinely for training, a HBEP is provided. This is a pragmatic approach to the delivery of an exercise programme for all patients, including those who live rurally or remotely from exercise centres. The use of patient activity trackers, frequent patient contact, exercise logbooks and motivational reviews will aim to maximise patient compliance. Although heterogeneity exists including home-based and centre-based exercise programmes, this could be a sustainable model for prehabilitation of surgical-oncology patients in the future.

PERIOP-OG provides a comprehensive programme to examine a strategy of peri-operative exercise in oesophagogastric cancer patients undergoing neoadjuvant treatment followed by curative surgery. This trial will be the first to examine the outcomes of peri-operative exercise training in this patient cohort. The interventions studied are easily reproducible and may provide a standardised framework for the prescription of exercise in oesophagogastric cancer patients.

## Trial status

The trial registration number is ClinicalTrials.govNCT03807518. Protocol Version 2 31 Oct 2019. The PERIOP-OG trial began recruitment on 1 March 2019. The anticipated end date is May 2020. To date 29 participants have been recruited.

## Data Availability

The datasets used and/or analysed during the current study will be available from the corresponding author on reasonable request.

## Abbreviations

NCT: Neoadjuvant chemotherapy
MDT: Multi-disciplinary team
6 MWT: 6-minute walk test
HRQoL: Health-related quality of life
LOT-R: Life Orientation Test-Revised
FACT-E: Functional Assessment of Cancer Therapy-Esophageal
GSE: General self-efficacy
PMS: Pearlin Mastery Scale
BMI: Body mass index
POMS: Post-Operative Morbidity Score
CD: Clavien-Dindo Classification
WCC: White cell count
CRP: C-reactive protein
QALY: Quality-adjusted life year
NMB: Net monetary benefit
SPIRIT: Standard Protocol Items-Recommendations for Interventional Trials
CBEP: Centre-based exercise programme
HBEP: Home-based exercise programme
REP: Rate of perceived exertion
